## **8. Safety Evaluation**

### **8.1 Adverse Events (AE)**

The time required to answer the questionnaire is approximately 5 minutes each time, which may cause mental distress or time constraints.

### **8.2 Serious Adverse Events (SAE)**

Not anticipated.

### **8.3 Procedures for Collecting, Recording, and Reporting AE/SAE**

Not anticipated.

### **8.4 Follow-up of Patients After the Occurrence of Adverse Events and Health Damage Compensation**

Health Damage Compensation: None

In this study, the safety of patients will be ensured by fully considering the contents described in "8.1 Adverse Events." If medical care is needed due to an adverse event, the subject will be informed, and appropriate medical care will be provided. In addition, an emergency response system will be in place to address unforeseen incidents.

## **9. Statistical Analysis**

### **9.1 Number of Registered Cases**

A total of 50 cases will be assigned to either the ePRO response group or the non-response group.

Basis: The number of participants was determined based on the number that can be registered within the set research period by the research group. Therefore, no power analysis was conducted.

### **9.2 Analysis of Results**

Analyses will be performed using multivariate analysis, unpaired t-tests, etc.

### **9.3 Significance Level**

A two-sided significance level of 5% will be used for hypothesis testing. When calculating confidence intervals, a two-sided 95% confidence interval will be applied.

### **9.4 Trial Termination Criteria**

The principal investigator will consider the continuation of the study based on the implementation

plan of the medical institution in the following cases:

If changes to the implementation plan are required, and the medical institution cannot accommodate these changes.

If the head of the medical institution gives instructions for modifications based on the opinion of the ethics committee, and the principal investigator does not accept these modifications.

If the ethics committee states that the study should not continue, and the head of the medical institution instructs the study to be terminated.

If the responsible physician is changed due to reasons such as transfers, and the new responsible physician cannot continue the study until they are able to do so (suspension).

### **9.5 Handling of Trial Data**

To strictly manage and adequately protect the personal information of participants, the data handled in this study will be anonymized using a correspondence table and used only as information that cannot identify specific individuals. During data analysis, personal information such as addresses and names will not be handled. The correspondence table linking participants with their newly assigned anonymized IDs will be strictly managed by the personal information manager of this study. When publishing the research results, personal information will not be disclosed. Chubu Electric Power Company will provide the cloud system for collecting ePRO and survey responses, as well as obtaining electronic consent, solely for research purposes. They will not analyze or use the data beyond the scope agreed upon for this study. Researchers will download the data from the system, store and manage it within the institution for research purposes, and analyze the data accordingly.

### **9.6 Deviations from the Statistical Analysis Plan**

Any results derived from analyses that deviate from the initial statistical analysis plan will be clearly explained.

### **9.7 Analysis Population**

The primary and secondary endpoints in this study will be analyzed using the largest analysis cohort, the full analysis set (FAS), as the main analysis.

## **10. Direct Access to Source Data and Documents**

The source data will be electronic data downloaded for research and analysis purposes. Direct access to the source data and documents will be permitted during review by the ethics review committee.

## **11. Monitoring and Auditing**

None.

## **12. Ethics**

The study will be conducted in accordance with the Declaration of Helsinki and the Ethical Guidelines for Life Sciences and Medical Research Involving Human Subjects.

### **12.1 Informed Consent**

Informed consent will be obtained electronically from the research subjects themselves before conducting the study. Specifically, healthcare professionals involved in this study will conduct face-to-face "identity verification," "confirmation that the selection, exclusion, and discontinuation criteria are met," and "selection of the appropriate questionnaire based on the subject's symptoms (AFEQT for atrial fibrillation, KCCQ for heart failure, SAQ for angina)" within the hospital. They will register the basic information (name, patient ID number, type of questionnaire, etc.) of the potential subjects into the "Smart Pro (tentative name)" system.

Next, the potential subjects will review the explanation document and consent item list of this study on their personal page linked to the basic information registered in the "Smart Pro (tentative name)" system, and after understanding them, they will complete the electronic informed consent procedure by checking the checkboxes for the explanation items and pressing the consent button based on their free will.

After the study begins, the responsible physician and other medical professionals involved in this study will inform the subjects how to access the electronic materials related to the explanation and consent content they received and agreed to. They will also provide information on how to contact the consultation office (established at the study office) for any inquiries related to the study and the consent withdrawal procedure.

If consent withdrawal occurs after study participation, the study office will instruct Chubu Electric Power to modify the data accordingly. This instruction does not include the deletion of operational log data necessary for addressing system failures or incidents, but the data will be rendered unviewable on the system screens. The update result of data deletion will be confirmed by a screenshot report from Chubu Electric Power. Chubu Electric Power will update the data stored in the "Smart Pro (tentative name)" system according to the instructions and receive confirmation of the implementation from the study office. The office established at the study office for inquiries is described in "12.4 Handling

Inquiries from Participants and Their Associates."

#### **12.1.1 Consent by a Representative**

Reasons for requiring cooperation through a representative: Not applicable

Selection policy for representatives: Not applicable

Explanation items to representatives: Not applicable

#### **12.1.2 Informed Assent**

Not applicable

### **12.2 Reporting to the Head of the Research Institution**

Annual reports and reports of suspension, termination, or completion will be made in accordance with the ethical guidelines.

### **12.3 Disclosure of Research Information**

The clinical trial will be registered with UMIN.

### **12.5 Conflict of Interest**

The costs required for this study will be covered by the Sports Medicine Comprehensive Center laboratory expenses, JST research funds, and AI Hospital project funds. "Smart Pro (tentative name)" is provided free of charge by Chubu Electric Power Company, and no financial support is received. A joint research agreement will be signed with Chubu Electric Power Company. The conflict of interest management committees of each research institution will determine whether fair research can be

conducted.

## **12.6 Post-Study Arrangements for Participants**

None

## **12.7 Handling Significant Genetic Findings**

Not applicable

## **13. Handling and Record Preservation of Data and Samples**

Data will be stored on personal computers (password-protected) in the Department of Cardiovascular Medicine and Sports Medicine Comprehensive Center (with locking facilities). The data will be kept for at least five years from the date of the research completion report or three years from the final research result report, whichever is later. After that, the obtained data will be stored on a dedicated PC after unlinkable anonymization, confirming that there is no information identifying individuals, with the responsible researcher and the personal information manager. The correspondence table used for anonymization will be completely deleted from the hard disk. If the data can be stored and managed within the locked personal computers in the Department of Cardiovascular Medicine and Sports Medicine Comprehensive Center before the five-year or three-year period mentioned above, the data in the Chubu Electric Power research system can be deleted.

### **13.1 Possibility of Using Data and Samples in Future Research and Providing Them to Other Institutions**

Not applicable

## **14. Economic Burden and Other Measures for Participants**

There is no economic burden. Insurance and other measures are not applicable.

## **15. Arrangements for Publishing Research Results**

During the analysis, data will be separated from personal identifiers, and when publishing research results, personal identification will not occur.

## **16. Addendum**

Not applicable

### **Revision History:**

Ver1.0 Created on April 28, 2022

## **1. Study Objective**

To investigate whether visualizing patient health status with electrical Patient-Reported Outcome (ePRO) monitoring for cardiovascular patients improves patient satisfaction.

### **1.1. Primary endpoint**

Patient satisfaction calculated by Likert-Scale

### **1.2. Secondary endpoint**

1. Assessment of well-being, patient preferences for shared decision-making using questionnaires.
2. Qualitative assessment of ePRO monitoring in ePRO group.

### **1.3. Exploratory endpoint**

Factors associated with improved patient satisfaction in ePRO group

### **1.4. Safety Evaluation**

The time required to answer the questionnaire is approximately 5 minutes each time, which may cause mental distress or time constraints.

### **1.5. Sample size**

Target Sample Size: 50 subjects (25 subjects  $\times$  2 groups)

Because this was a pilot randomized controlled trial, formal sample size calculations were not performed.

## **2. General Considerations in Statistical Analysis**

### **2.1. Interim Analysis**

No interim analysis will be conducted.

### **2.2. Data Monitoring Committee**

A Data Monitoring Committee will not be established. Decisions regarding data handling will be made through consultation between the Principal Investigator and the Lead Statistician.

### **2.3. Summary Statistics**

For continuous variables, the following summary statistics will be provided: sample size, mean, median, standard deviation, minimum, 25th percentile, 75th percentile, and maximum. For categorical variables, the sample size, frequency, and percentage will be reported.

### **2.4. Significance Level and Confidence Interval**

A two-sided significance level of 5% will be used for hypothesis testing. When calculating confidence intervals, a two-sided 95% confidence interval will be applied.

### **2.5. Adjustment for Multiplicity**

No adjustment for multiplicity will be applied in the analyses of efficacy and safety.

### **2.6. General Rules for Data Handling**

#### **【Rules for Calculating Days and Periods】**

- Unless otherwise specified, the number of days will be calculated by subtracting the start date from the end date and adding 1.
- When converting days into years, months, or weeks, 1 year will be considered as 365.25 days, 1 month as 30.4375 days, and 1 week as 7 days.

#### **【Rules for Significant Figures】**

- For mean, standard deviation, median, and interquartile range, one decimal place lower than the raw data will be used (i.e., round off the second decimal place).
- Maximum and minimum values will retain the same number of decimal places as the raw data.
- Percentages will be displayed to one decimal place (e.g., 12.3%), rounding off the second decimal place.
- When calculating statistical measures such as mean, standard deviation, or median, rounding will not be applied during intermediate calculations; only the final result will be rounded.
- P-values will be reported to three decimal places (rounding the fourth decimal place). If rounding results in a value of 0.000, it will be displayed as  $< 0.001$ .

## **2.7. Data Handling**

In principle, data handling decisions will be made by the Principal Investigator. If questions or uncertainties arise, the final decision will be made in consultation with the Lead Statistician. The handling of missing values and variable transformations is outlined below:

- **Missing Data:** No special statistical imputation methods will be applied to missing data. An unpaired t-test will be performed on complete data excluding missing data.
- **Outlier Data:** The handling of outlier data will be determined by the Data Handling Committee (comprising the Principal Investigator and the Lead Statistician).
- **Variable Transformation:** If variable transformations (e.g., square root or logarithmic transformations) are applied, details will be documented in the "Analysis Results Report."

## **2.8. Amendments to the Statistical Analysis Plan**

Modifications to the study protocol that require changes to this Statistical Analysis Plan will result in a revised plan, with details of the amendments recorded in the "Revision History of the Statistical Analysis Plan."

## **2.9. Final Analysis**

The final analysis will be conducted only after data has been obtained for all cases and both cases and data have been locked. Statistical analysis will not be conducted prior to this point. The Lead Statistician will compile the "Analysis Results Report" and submit it to the Principal Investigator for approval.

## **3. Study method**

In this study, participants will be randomly assigned to ePRO monitoring or usual care. We will explain this research face-to-face to the patients and obtain electronic consent. Prior to randomization, patients with HF, AF or CAD will be assigned to KCCQ-12, AFEQT or SAQ respectively. For patients with two or more of these three coexisting cardiovascular diseases, treating physicians will assign an appropriate PRO measure based on their primary cardiovascular disease. Participants will be randomly assigned to ePRO group or control group. After randomization, they are instructed to respond to the questionnaires for outcome assessment. Patients assigned to ePRO group are also asked to respond to physician assigned PRO measures.

All patients will be followed up on an outpatient basis every 4 weeks ( $\pm 2$  weeks) for a total of 5 visits. At every visit, patients in the ePRO group will receive a smart tablet and answer for the

assigned questionnaire (KCCQ-12, AFEQT or SAQ) before entering the examination room. The reports of PROs will be displayed on smart tablets and shared between physicians and patients during medical examination. Patients in the control group received standard care in accordance with the latest clinical guidelines. All patients will be asked to respond to the questionnaires for outcome assessment at the fifth visit

#### **4. Analysis Cohort**

The primary and secondary endpoints in this study will be analyzed using the largest analysis cohort, the full analysis set (FAS), as the main analysis, applying an intention-to-treat approach. Sensitivity analysis will be conducted using the per-protocol set (PPS), a cohort adhering strictly to the study protocol, if necessary.

##### **4.1. Full Analysis Set (FAS)**

The FAS will include all subjects enrolled in this study. However, data from subjects with significant protocol violations (e.g., lack of consent, enrollment outside the contract period, or absence of efficacy data) will be excluded.

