### **5.3 Discontinuation Criteria**

The principal investigator or sub-investigators will discontinue the study for a subject if any of the following conditions are identified after subject registration:

- (1) An adverse event occurs, and the principal investigator or sub-investigators determine that the study should be discontinued.
- (2) The subject requests to withdraw from the study.
- (3) It is determined that the subject is inappropriate for inclusion in the study.
- (4) It becomes evident that the necessary observations and tests cannot be conducted due to the subject's circumstances.
- (5) Any other reason where the principal investigator or sub-investigators judge that the collection of questionnaire data should be discontinued.

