### **Reasons for Settings:**

- (1) was established to ensure safety considerations.
- (2) and (3) was set as part of the informed consent process, acknowledging the subjects' rights.
- (4) was established because subjects who cannot undergo necessary observations should be withdrawn from the study promptly.
- (5) was set in consideration of any other situations requiring the discretion of the principal

investigator or sub-investigators to discontinue the study.

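### The main analysis is labelled intention-to-treat, but it covers only patients with both a baseline and a final satisfaction score, and no planned sensitivity analysis tests that restriction

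*Combined protocol and SAP*

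**What the plan says.** Protocol section 9.7 and SAP section 4 make the FAS the main analysis set, and the SAP adds that it is analysed "applying an intention-to-treat approach". SAP section 4.1 starts broadly ("The FAS will include all subjects enrolled in this study") and then removes patients with significant protocol violations, giving as examples "e.g., lack of consent, enrollment outside the contract period, or absence of efficacy data) will be excluded".

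On missing values, SAP section 2.7 states "No special statistical imputation methods will be applied to missing data" and then "An unpaired t-test will be performed on complete data excluding missing data". SAP section 6.1 compares mean change in satisfaction from baseline to final follow-up. SAP section 3 places the outcome questionnaires after randomisation and at the fifth visit. The only sensitivity analysis is the per-protocol set, to be run if needed (SAP section 4). SAP section 4.2 draws that set from within the FAS.

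Protocol section 5.3 lists reasons for discontinuing the study for a subject. They include "It is determined that the subject is inappropriate for inclusion in the study" and, as a catch-all, the investigator's judgement that questionnaire collection should stop. The rationale printed beneath the list says "subjects who cannot undergo necessary observations should be withdrawn from the study promptly". No section says whether the outcome is still sought from a discontinued patient.

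**The concern.** Having no outcome data is a result of follow-up. It arises after randomisation and may depend on the arm. Section 4.1 nevertheless lists it beside lack of consent, as if it were an entry violation. An analysis that drops such patients no longer compares the groups that were randomised, whatever its label.

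The setting makes uneven loss plausible. The trial is open label (protocol section 4.4). Only the ePRO arm completes a disease-specific questionnaire on a tablet at every visit (protocol section 4.2). The one harm the protocol foresees is distress or time pressure from answering (section 8.1). The primary outcome is satisfaction, so a patient who finds the process tiresome could be both less satisfied and more likely to be missing. The first outcome questionnaire also follows randomisation, so even a baseline score can be lost once allocation is known. With 25 per arm, each lost patient is 1/25 = 4% of the arm.

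**Working it through.** **Step 1: who contributes to the primary test.**
- Section 4.1 removes patients with no efficacy data.
- A patient with a baseline score only may arguably stay in the FAS, but has no change score for section 6.1, and section 2.7 then drops that patient.
- A patient with a final score only is dropped in the same way.
- On either reading, the analysed set is the patients with both scores.
- The per-protocol set is FAS minus further patients, so it cannot restore anyone already removed.

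**Step 2: inputs.** From the documents: 25 × 2 = 50 patients (SAP section 1.5, which agrees with protocol section 9.1), and a two-sided 5% unpaired t-test (SAP sections 2.4 and 6.1). The plan gives no power, SD, effect size or dropout rate, so it has no figure of its own to reproduce beyond that product. Assumed:
- k1 and k0 patients are lost in the ePRO and control arms;
- the change score has SD 1 among those retained;
- lost patients' mean change is g SD worse than that of retained patients in the same arm;
- there is no true difference among all randomised patients.

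**Step 3: formulas.**
- Bias = g × (k1 − k0)/25.
- SE = √(1/n1 + 1/n0), with n1 = 25 − k1 and n0 = 25 − k0.
- The rejection rate comes from the noncentral t distribution with n1 + n0 − 2 degrees of freedom and noncentrality bias/SE.

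For example, 8 v 0 lost with g = 1 gives bias = 8/25 = 0.32, SE = √(1/17 + 1/25) = 0.314, noncentrality 1.02 and rejection 16.9%.

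**Step 4: results.**

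| Lost, ePRO v control | Bias, g = 0.5 | Rejection | Bias, g = 1 | Rejection |
|---|---|---|---|---|
| 3 v 3 | 0 | 5.0% | 0 | 5.0% |
| 3 v 0 | 0.06 SD | 5.5% | 0.12 SD | 6.9% |
| 5 v 1 | 0.08 SD | 5.8% | 0.16 SD | 8.1% |
| 5 v 0 | 0.10 SD | 6.2% | 0.20 SD | 10.0% |
| 8 v 2 | 0.12 SD | 6.6% | 0.24 SD | 11.3% |
| 8 v 0 | 0.16 SD | 7.9% | 0.32 SD | 16.9% |

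Losses of 3, 5 and 8 are 12%, 20% and 32% of an arm. Simulated t-tests agree with these rates to within a few tenths of a percentage point. At a rounded bias of 0.30 SD, the 8 v 0 rate is about 15–16%.

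**Step 5: precision only.** With equal loss of similar patients, the 95% interval half-width rises from 0.57 SD at 25 per arm to 0.61 SD at 22 and 0.64 SD at 20. The difference detectable with 80% power rises from 0.81 to 0.87 and 0.91 SD.

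**The case against.** The strongest reply is that section 4.1, read narrowly, removes only patients with no score at all, whom no observed-data t-test could use. Patients who were ineligible or adhered poorly but answered both questionnaires stay in the FAS and leave only the per-protocol set. This stands: the main analysis is not a per-protocol analysis. The complete-case rule still produces the restriction, and the intention-to-treat label is still wrong.

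Four stronger readings are tempting, and the documents do not support them.

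- **That discontinued patients certainly stop being followed.** Section 5.3 discontinues the study for the subject, but only its last item mentions questionnaire collection. The general schedule says all patients are asked at the fifth visit. The text is silent on discontinued patients, so this is a gap and not a stated rule.
- **That low satisfaction scores would be removed as outliers.** Section 2.7 says "The handling of outlier data will be determined by the Data Handling Committee (comprising the Principal Investigator and the Lead Statistician". The rule covers all data, including laboratory values, and nothing singles out Likert responses. SAP sections 2.9 and 8.3 also require data lock, subject-handling criteria and data review before analysis.
- **That the bias must favour ePRO.** Control patients disappointed by their allocation may also leave. The burden statement names no arm, and protocol section 4.3.2 has questionnaire data collected five times without distinguishing arms. Patients unable to use tablets are excluded at entry (protocol section 5.2).
- **That the error rate is known to be three times nominal.** That needs heavy loss in one arm only and a full 1 SD gap.

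It is also fair that this is a pilot with no power claim, and that SAP section 5.1 will count dropouts, discontinuations and analysed cases. Those counts describe the loss, although a split by arm is not stated. They do not show what the loss does to the estimate. The plan still sets a 5% test on whether ePRO improves satisfaction.

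**Conclusion.** The concern holds in this form. The primary analysis is a complete-case analysis of patients with both scores, it is wrongly labelled intention-to-treat, and nothing in the plan tests the effect of the exclusions. The contradiction between SAP sections 4, 4.1 and 2.7 is on the page and rests on no assumption.

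The size does rest on assumptions. Across the scenarios shown, the bias runs from 0 to 0.32 SD and the false-positive rate from 5% to about 17%. The upper end needs 8 patients lost in one arm, none in the other, and a 1 SD gap. Moderate imbalance (5 v 1) gives about 6–8%. The documents supply no dropout rate or SD to narrow this, and they do not fix the direction.

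Severity: should be fixed. The small sample, the pilot status and the absence of a power claim keep it below the level of a critical defect.

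**What to change.** 1. **SAP section 4.1.** Define the FAS as all validly consented randomised patients, analysed as assigned, and delete absence of efficacy data as an exclusion. If the sponsor prefers the present set, drop the intention-to-treat label and call the analysis complete-case.
2. **Protocol section 5.3.** State that stopping ePRO, or being discontinued, does not end outcome collection, and request the visit-5 questionnaire from everyone who has not withdrawn consent. This concerns data collection only; the discontinuation criteria are untouched. Where consent is withdrawn, protocol section 12.1 has the stored data modified and made unviewable, so report those patients as a count by arm.
3. **SAP sections 2.7 and 5.1.** The complete-case t-test may stay as the primary test if its missing-data assumption is stated. Report missing baseline and final scores, with reasons, by arm. Prespecify one sensitivity analysis that includes all randomised patients, for example multiple imputation with a delta shift on imputed ePRO-arm scores, from 0 to 1 SD. Because the direction is unknown, the same shift can be shown for control. A repeated-measures model is an option only if satisfaction is collected at all five visits, on which protocol section 4.3.2 and SAP section 3 differ.
4. **SAP section 4.3.** Make subject-exclusion decisions before lock, on a listing without treatment codes.

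The cost is revised SAP wording, a short protocol clarification, a few extra tables, some effort to reach discontinued patients, and a somewhat wider interval in the sensitivity analysis. No change in sample size is needed.
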